**Methods:**

The sample size of this randomized, controlled trial has been set to a total of 400 participants with substance-related problems. Participants living in Stuttgart, Germany, will be randomly allocated to (1) the intervention group with immediate online assessment and subsequent sector-independent treatment coordination (ASSIST) or (2) the waitlist group. Participants in the waitlist group will initially remain in usual care and only be provided with the online assessment 6 months later. Short-term effects (over 2 months) and medium-term effects (over 6 months) of ASSIST will be compared between the intervention and the waitlist groups. The primary outcome is improved treatment satisfaction. Secondary outcomes include improved subjective quality of life and empowerment, reductions in patients’ substance use, unmet needs and illness-related clinical and social impairment. Health economic evaluation as well as quantitative and qualitative process evaluations will be conducted.

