### Outcomes {12}

#### Primary outcome

The primary outcome is the mid-term change in satisfaction with substance-related care over 6 months. With the increasing emphasis on patient engagement and continuous quality improvement in mental health care, evaluation has shifted to measuring the performance of a treatment programme in terms of treatment satisfaction [27]. Treatment satisfaction represents an important indicator of patient benefit [28]. The German short version of the Client Satisfaction Questionnaire (CSQ-8) [29], called the ZUF-8 Questionnaire [30], will be used every 2 months (t0, t1, t2, t3 and t4 if applicable).

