#### Secondary outcomes

The secondary outcomes are participant’s empowerment, quality of life, perceived needs, functioning, clinical and psychological impairment and severity of substance use. These will be assessed at t0, t1, t3 and t4. Further secondary outcomes are frequency of substance use, craving, somatic symptoms, depression and anxiety. These are measured twice, at t0 and t3. The tools used to measure the secondary outcomes are as follows:Assessment of Empowerment in Patients with Affective and Schizophrenic Disorders (EPAS) [31]: The EPAS questionnaire measures empowerment as the patient’s perceived possibilities to control his or her own life on five dimensions: daily living, social relationships and sexuality, treatment participation, self-efficacy and self-esteem. This self-report questionnaire has 33 items and five additional items each for patients who are employed and for patients with minor children.Euro Quality of Life - 5 Dimensions (EQ-5D) [32]: The EuroQol (EQ-5D-5L) is used to assess health states as a basis for determining quality-adjusted life years (QALY).World Health Organization Quality of Life - Short Version (WHO-QoL-BREF) [33]: The WHOQOL-BREF captures the substance user’s subjective quality of life on the dimensions of physical health, mental well-being, social relationships and environmental conditions. The WHOQOL-BREF is a self-report questionnaire with 25 items.Camberwell Assessment of Need - European Version (CAN) [34]: The CAN is a rating instrument to record PWUS’s perceived needs and the extent to which they are met, covering 23 areas.World Health Organization Disability Assessment Schedule (WHODAS 2.0) [35]: The 12-item WHODAS 2.0 is a valid, reliable self-report instrument for the assessment of functioning and generic disability [36].Health of the Nation Outcome Scale (HoNOS) [37, 38]: The HoNOS is a 12-item rating instrument to assess clinical and psychosocial impairment of people with mental disorders in four categories: behaviour, impairment, symptoms and social functioning.Severity of Dependence Scale (SDS) [39]: The SDSs are 5-item screening questionnaires measuring the severity of dependence on alcohol and drugs.Timeline Follow Back [40, 41]: The calendar method, called Timeline Follow Back, is used to get an estimate of the participant’s daily patterns and frequency of substance use over 7 days.Mannheim Craving Scale (MaCS) [42]: The MaCS Questionnaire, consisting of 12 items and 4 additional items, measures obsessive-compulsive symptoms in the context of substance abuse and dependence.Somatic Symptom Scale (SSS-8) [43, 44]: The 8-item Somatic Symptom Scale (SSS-8) was used as a brief, patient-reported outcome measure of somatic symptom burden.Patient Health Questionnaire (PHQ-4) [45]: The Patient Health Questionnaire is a 4-item measure to screen for depression.Generalized Anxiety Disorder Scale (GAD-7) [46]: The Generalized Anxiety Disorders Scale is a 7-item screening tool for detecting generalized anxiety disorder.Perceived Stress Scale (PSS-10) [47, 48]: The 10-item Perceived Stress Scale was used to assess perceived psychological stress.

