### Sample size {14}

Assuming a simplified statistical model (repeated measures design with within (time) × between (group) interaction, 2 groups, 4 time points) and a dropout rate of 40%, a sample size of 400 subjects allows the detection of an effect with a moderate effect size (Cohen’s *f* = 0.25 [50]) for the primary outcome (change in satisfaction (ZUF-8 Score) over 6 months) at a significance level of *p* < 0.05 with a power ≥ 0.90, as calculated by means of G*Power 3.1 [51].

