## Statistical methods

### Statistical methods for primary and secondary outcomes {20a}

The analysis of the primary and secondary outcomes will follow the intention-to-treat (ITT) principle. Mixed models with fixed time effects and time × group interaction effects (fixed: time (4 or 2 time points), group (2 groups), time × group interaction; random: patient) will be applied. The time by group interaction will reflect the intervention effect.

The cost-effectiveness ratios from the perspectives of the national economy will be determined using the net benefit method.

Furthermore, for the waitlist group, the changes in the primary and secondary outcomes criteria during the waiting period (from t0 to t1) and after the assessment and treatment coordination (from t3 to t4) are compared using a paired *t*-test.

Implementation of sector-independent treatment coordination starting from an online assessment is evaluated mainly using descriptive methods (relative frequencies and measures of agreement). These methods are also used to show the extent to which treatment recommendations based on the online assessment and the interview at the Regional Competence Centre differ from each other and the extent to which actual treatment pathways match the recommendations. Fit is classified as less than adequate (treatment intensity lower than recommended), adequate (treatment intensity as recommended) and more than adequate (treatment intensity higher than recommended). The factors that influence fit and the extent to which fit affects the outcomes are also examined.

The statistical significance level will be set at *p* < 0.05. The statistical programmes IBM SPSS 25, STATA 15 and SAS 9.4 will be used for statistical analysis.

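### The primary outcome is the 6-month change in satisfaction, but the named and powered test is a four-visit time × group interaction that is not specific to 6 months

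*Protocol article*

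**What the plan says.** Under Primary outcome, the protocol states: "The primary outcome is the mid-term change in satisfaction with substance-related care over 6 months". The ZUF-8 "will be used every 2 months (t0, t1, t2, t3 and t4 if applicable"). The abstract's Methods separates two horizons: "Short-term effects (over 2 months) and medium-term effects (over 6 months) of ASSIST will be compared between the intervention and the waitlist groups". Mid-term therefore most naturally means t0 to t3.

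Under Statistical methods {20a}, the mixed model is specified as "fixed: time (4 or 2 time points), group (2 groups), time × group interaction; random: patient) will be applied", followed by "The time by group interaction will reflect the intervention effect".

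Under Sample size {14}, the power claim (at least 0.90 for f = 0.25, 400 participants, 40% dropout) is for a "repeated measures design with within (time) × between (group) interaction, 2 groups, 4 time points".

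For the first group of secondary outcomes the schedule reads "These will be assessed at t0, t1, t3 and t4"; the remaining ones are taken at t0 and t3. Under Participant timeline {13}, t4 is reached only by the waitlist group.

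The article names no t3-versus-t0 group contrast, no linear slope and no direction of effect for the primary test.

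**The concern.** The outcome is a change over one interval; the named effect is a difference in pattern over four visits. An interaction with categorical time rejects for any non-parallel pair of profiles. That includes an early gain that has gone by 6 months, and it includes a pattern favouring the waitlist arm. The outcome is described as improved satisfaction, yet the test has no direction and yields no single estimate with a confidence interval.

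At stake is what counts as trial success. The Discussion plans to extend ASSIST to other communities if results are positive. If the interaction is significant and the arms do not differ at 6 months, the plan as written gives no rule for whether that is positive.

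**Working it through.** **Inputs from the protocol.** 400 randomised 1:1 and 40% dropout, so N = 400 × 0.6 = 240 completers (120 per arm); 2 groups; 4 time points; f = 0.25; two-sided α = 0.05.

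**Assumptions, not in the protocol.** Unit SD at each visit, compound symmetry (as a random patient intercept implies) with correlation ρ = 0.3, 0.5 or 0.7, time categorical, complete data for the 240, and the mean profiles below.

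**1. The stated power.** Numerator df = (4 − 1)(2 − 1) = 3; denominator df = (240 − 2) × 3 = 714. With the smallest noncentrality tried, λ = N·f² = 240 × 0.0625 = 15, power is 0.915. With λ = N·m·f²/(1 − ρ), where m = 4 is the number of time points, and ρ = 0, λ = 60 and power exceeds 0.999. The claim of at least 0.90 is reproduced, and it belongs to the 3-df interaction.

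**2. Formulas for the comparison.** Let d be the group differences at t0 to t3 in SD units.
- Interaction: λ = (N/4) × Σ(dⱼ − mean d)² / (1 − ρ), referred to a noncentral F on 3 and 714 df.
- Contrast: (d₃ − d₀)/SE, with SE = √[2(1 − ρ) × 4/N], using the normal formula. SE = 0.153, 0.129 and 0.100 at ρ = 0.3, 0.5 and 0.7.

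**3. No difference at 6 months.** For d = 0, 0.4, 0.2, 0 the mean is 0.15 and the sum of squares is 0.0225 + 0.0625 + 0.0025 + 0.0225 = 0.11. At ρ = 0.5, λ = 60 × 0.11/0.5 = 13.2.

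| Profile (t0/t1/t2/t3) | Test | ρ = 0.3 | ρ = 0.5 | ρ = 0.7 |
|---|---|---|---|---|
| 0/0.4/0.2/0 | interaction | 0.731 | 0.874 | 0.985 |
| 0/0.2/0.1/0 | interaction | 0.22 | 0.30 | 0.48 |
| either | t3−t0 contrast | 0.05 | 0.05 | 0.05 |

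A simulation of 4,000 trials with a more sustained transient (0/0.4/0.4/0, ρ = 0.5) agrees with the formulas: the interaction was significant in 96.9%, the contrast in 4.4%, and the interaction without the contrast in 92.5%.

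**4. A real difference of 0.4 SD at 6 months, ρ = 0.5.** The contrast has power 0.87 whatever the path.

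| Path to 0.4 SD | Interaction | t3−t0 contrast |
|---|---|---|
| Steady linear rise | 0.79 | 0.87 |
| Constant from t1 | 0.90 | 0.87 |
| Only at t3 | 0.90 | 0.87 |
| 0/0/0.2/0.4 | 0.87 | 0.87 |
| 0/0.2/0.4/0.4 | 0.87 | 0.87 |

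**5. What 240 completers give for the contrast.** The difference detectable with 90% power is (1.960 + 1.282) × SE = 0.50, 0.42 and 0.32 SD at ρ = 0.3, 0.5 and 0.7.

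**6. Visit counts.** Four points fit the primary outcome (t0 to t3) and two fit the secondary outcomes at t0 and t3. The set scheduled at t0, t1, t3 and t4 has three visits common to both arms, a count that "fixed: time (4 or 2 time points), group (2 groups") does not cover.

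**The case against.** The strongest reply is that the protocol can be read consistently: change over 6 months may mean change across the whole course, which a four-visit interaction addresses and on which the trial is sized. The abstract's separation of 2-month from 6-month effects favours the endpoint reading, but the primary outcome section does not spell out t3 minus t0.

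No degrees of freedom are printed, and in the same model the group × t3 coefficient, with t0 as reference, is the 6-month contrast. An analysis plan that is not shown might name it. That is possible. But this protocol names the interaction as the effect and powers it, so choosing the contrast later would change the primary test. Linear time is not indicated, and a slope is still not the t3−t0 change.

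The fading profile is assumed. Nothing predicts it: the intervention description includes continued accompaniment and plan adjustment. The rejection rate also falls steeply when the profile is halved. Both remarks stand; the figures illustrate non-specificity and are not a forecast.

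Three stronger readings are tempting and unsupported:
- That the interaction is no test of the 6-month change. Its joint null includes equal 6-month change, and it has good power when that change differs.
- That the planned test is generally underpowered. Of the paths tried, only the steady linear rise shows a material loss.
- That post-crossover t4 data enter the randomised comparison. Nothing says so; {20a} gives t4 its own paired t-test within the waitlist group.

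**Conclusion.** The point holds as a mismatch between the outcome and the test. With categorical time, as the wording on time points implies, the named effect is a valid 3-df test without direction, sensitive but not specific to 6 months. A significant result alone would not establish improved satisfaction at 6 months. The size depends on assumptions: 73% to 98% significant interactions for a transient 0.4 SD gain, and 22% to 48% for half of it, against 5% for the contrast, over ρ from 0.3 to 0.7 under compound symmetry with 240 completers. Power against real 6-month effects is otherwise similar for the two tests, apart from the linear case. The stated power is not wrong; it refers to the interaction. The missing three-visit case is a minor wording gap affecting secondary outcomes only.

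**What to change.** Name as the single primary test the model-based group difference (intervention minus waitlist) in t3−t0 change in ZUF-8, two-sided at 5% with its 95% confidence interval, from the same mixed model with categorical time. Make the 2-month contrast and the overall interaction supportive. Restate the power under Sample size {14} for that contrast, with the assumed within-person correlation given.

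For the secondary outcomes scheduled at t0, t1, t3 and t4, state three common time points (t0, t1, t3), and say that t4 is used only in the within-waitlist comparison.

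The cost is wording in the protocol and analysis plan plus one recalculated power statement; no new data are needed. The small downside is that an effect present only at t1 or t2 would no longer count as primary success.

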### Interim analyses {21b}

No interim analyses are planned.

### Methods for additional analyses (e.g. subgroup analyses) {20b}

Substance-specific effects (legal vs. illegal substances) will be examined using mixed-effect models extended by the interaction effect of time × treatment × substance group.

An in-depth analysis should reveal effects in subgroups (e.g. legal or illegal substance use, individuals with a little or a lot of experience with services or PWUS with specific treatment goals).

### Methods in analysis to handle protocol non-adherence and any statistical methods to handle missing data {20c}

In addition to the main analyses and in order to assess the maximal intervention efficacy in ideal conditions, a per-protocol (PP) approach will be followed to analyse the primary outcome. The criteria for the PP population will be defined in the statistical analysis plan prior to data analysis and may include the following:Incomplete online assessment and/or Treatment Assistant.The time between study entry and appointment at the Regional Competence Centre is too long.Infrequent use of the online platform by participants in the intervention group or no use after the appointment at the Regional Competence Centre.Follow-up assessment (t3) being far outside the initially planned time periods, i.e. more than 2 months before or after the time point that is 6 months after baseline assessment (t0).Long-term absence (more than 4 weeks) from Stuttgart and the local addiction support system during the intervention.

No imputation of missing data will be needed for the main analysis via mixed linear models. For the sensitivity analysis, missing values will be handled using the fully conditional specification (FCS) method [53]. The number of imputations will be chosen based on the portion of missing values. Then, each of the completed datasets will be analysed using the proposed statistical method. According to Rubin’s rule [54], the final result will be the average result of all completed datasets.

### Plans to give access to the full protocol, participant-level data and statistical code {31c}

The full protocol (including the data-management and statistical-analysis plans) and the statistical code will be available on request from AMS. All data for which there is no conflict with data-protection regulations will be published with open access.

## Oversight and monitoring

### Composition of the coordinating centre and trial steering committee {5d}

MC and JR will oversee the whole project including the intervention and the communication between the funding agency and the project team. LS will coordinate the project management and the implementation of the intervention.

The evaluation team of Ulm University comprises ten persons: AMS, as principal investigator and biostatistician, will oversee the entire study process including data management and data analysis. EP will coordinate the evaluation and will provide peer perspective in the conduct of the study and the interpretation of findings. They will form the evaluation team together with two senior researchers (TB and RK) and seven junior researchers (CG, JL, TBA).

The trial-steering committee consists of AMS and TB from the evaluation centre, as well as MC and JR as representatives of the sponsoring team.

### Composition of the data monitoring committee, its role and reporting structure {21a}

The evaluation team of Ulm University, that is independent from the sponsor, will monitor the data. Given the non-adaptive design, the rather short study period and the low probability for serious adverse events (SAEs), no interim analyses are needed and the need for preterm determination of the study is unlikely. No independent data monitoring committee was established for these reasons.

### Adverse event reporting and harms {22}

No adverse events caused by the intervention are expected. Nevertheless, all SAEs occurring during the trial observed by the research associates, the service providers or reported by the participant, no matter the study arm they belong to, will be recorded in the case report form in SoSci Survey. The study participants will be requested (if possible) to immediately inform the responsible research associate about SAEs. The occurrence of SAEs will be reported, at the latest, at the next follow-up assessment.

### Frequency and plans for auditing trial conduct {23}

There are no plans for independent trial auditing. But, periodic audit procedures for study conduct and intervention will take place by the coordinating centre, the evaluation team and the trial steering committee. For this purpose, there is a sophisticated communication plan that includes 1st separate weekly team meetings of the coordinating team including the intervention team and the evaluation team, 2nd bi-weekly meetings of the project managers of the coordinating team (LS) and the evaluation team (EP) and 3rd quarterly meetings of the trial-steering committee. These meetings provide the opportunity to evaluate the progress of the study and obtain information about potential problems. There will be an annual report to the funding body on the course of the study, the obtained findings and the impact of deviations from the study protocol and of incidents during trial conduct.

Several procedures are implemented by the coordinating team to control the quality of the interventions within the local addiction support system as follows:Regular meetings with the project teamDiscuss and practise different the procedures and situations with the project teamRegular check-ups of the technical componentsEnsuring of the technical supportRegular contacts with local cooperation partnersInforming and supporting the teams of the care providersContacting study participants by the Regional Competence Center if information or feedback is missingAssessment of the fidelity criteriaRegular information of the cooperation partners about the current status of the studyRegular information of the city council

Regarding data integrity, a research assistant with training in data supervision will verify the consistency and completeness of data each month. In addition, this research assistant will conduct semi-annual monitoring visits with research assistants responsible for data collection. The research assistant will assure that data are accurate and in agreement with any paper source documentation used, verify that informed consent for study participation has been properly obtained and documented, confirm that participants entered into the study meet inclusion and exclusion criteria, verify that study procedures are being conducted according to the standardized operating procedures and monitor serious adverse event reporting.

### Plans for communicating important protocol amendments to relevant parties (e.g. trial participants, ethical committees) {25}

Any modifications to the protocol which may impact the study’s conduct or the potential benefit to the participants or which may affect participant safety will require a formal amendment to the protocol. Important protocol amendments must be submitted to local ethical committees and be communicated to all directly involved parties, specifically the sponsoring team, the employees at the Regional Competence Centre, the Institute for Epidemiology and Medical Biometry at Ulm University, the funder and if needed the participants and service providers. The entry at the German Clinical Trial Register DRKS00026996 will be updated accordingly.

### Dissemination plans {31a}

The dissemination plan follows best-practice recommendations and aims to engage with PWUS, service providers and the public to disseminate the findings across private and public fields. All collaborators are encouraged to contribute to the dissemination of findings. The research results will be disseminated in peer-reviewed journals as well as during international and national conferences. In addition, findings will be disseminated widely to all stakeholders via public platforms and social media. A project report in plain language will be sent to all participants and will be accessible on the project’s website.

## Discussion

ASSIST is a complex intervention that aims to overcome well-known issues and challenges of the German addiction support system (e.g. poor identification of substance users, inadequate networking between service providers, abstinence as a compulsory treatment goal, and unclear strategies to assign PWUS to addiction-specific treatment options) by combining established innovative approaches in mental health care. Based on an online assessment and sector-independent, indication-based and goal-specific treatment recommendations, PWUS will be assigned to appropriate services of the Stuttgart addiction support system. The individual and patient-centred Treatment Assistant, developed with input from the PWUS in the Regional Competence Centre, will be displayed on an online platform that facilitates treatment monitoring and collaboration across the different service providers.

This protocol sets out the methods for evaluating the impact of ASSIST as an extension to the existing care as usual in Stuttgart. Stuttgart is the capital of the federal state of Baden-Württemberg and is characterized by a large, diverse and professional addiction support system [55]. This RCT with a waitlist design and embedded process evaluation will help to gain knowledge about the effectiveness and cost-effectiveness of ASSIST, but also about implementation outcomes and determinants.

A major strength is the full-coverage cooperation with service providers of the entire region of Stuttgart, enabling treatment coordination across a wide range of services and levels of care. However, the SARS-CoV-2 pandemic and related contact restrictions have complicated the initiation and strengthening of cooperation during the pre-implementation phase. As ASSIST is a complex intervention relying on good networking with local service providers, the implementation success depends on each individual team member at local service providers and their willingness to engage themselves in the project. Thus, the low contact in the pre-implementation phase might impede the recruitment of study participants and the use of the Treatment Assistant by employees of cooperating facilities.

Another strength is that the effectiveness will be evaluated independently of the service providers by Ulm University conducting a RCT, the gold standard in effectiveness evaluation. Moreover, the prospective waitlist design allows for the evaluation of intra-individual changes under both conditions. On top of that, a comprehensive set of quantitative and qualitative data will be gathered to gain deep insights into implementation processes. As some of the scales to be used have not been validated yet in comparable conditions (e.g. the German version of the MATE-Q used during the intervention and the EPAS used as an outcome in PWUS), validity and intern consistency as reliability will be analysed as part of this study.

If the results of the current study are positive, it is planned to scale up ASSIST to other communities in Germany. The development of ASSIST more broadly will benefit from the extensive knowledge gained during the trial in terms of facilitators and barriers to sustainable implementation of a cross-sectoral care concept in substance use services. Finally, this randomized controlled trial will generate the first major body of evidence on the effectiveness and cost-effectiveness of sector-independent treatment coordination for people with substance-related disorders following an online assessment in Germany.

